#### 3.3 ARIC Study (Validation Cohort)

The Atherosclerosis Risk in Communities (ARIC) Study is a prospective U.S. cohort of men and women (15,792 participants at baseline, 1987–1989). For validation, we will use African-American ARIC participants with APOL1 high-risk genotype. Specifically, 314 African-American APOL1 high-risk individuals who attended visit 2 (1990–1992) were included. An additional 2021 African-American individuals with APOL1 low-risk genotype and 8,602 European ancestry APOL1 low-risk participants were included as external reference. Genotyping (TaqMan assays) and SomaScan proteomics (5K proteins) were available on visit-2 samples. Follow-up (ascertainment of outcomes) is truncated at 10 years from

visit 2 to harmonize with the PMBB analysis. All ARIC analyses were approved under study application MP4524.

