### **3.7 Statistical Analysis**

The APOL1–high-risk cohort will be randomly divided into an 80% training set and 20% test set (stratified by outcome incidence). In the training set, candidate proteins will be selected via an elastic-net penalized Cox proportional hazards regression (age, sex, baseline eGFR, and log2(UACR) included as unpenalized covariates). Tuning parameters ( $\alpha$ ,  $\lambda$ ) will be chosen by 8-fold cross-validation. The final APRS model will include the nine selected proteins plus the four clinical covariates. Model discrimination will be quantified

by time-dependent AUC (tAUC) at prespecified time points and Harrell's C-index. Model performance will be compared to the KFRE (4-variable equation) and established CKD risk scores.

Proportional hazards assumptions for APRS and covariates will be tested using Schoenfeld residuals. Sensitivity analyses will address potential biases: we will apply inverse-probability-of-censoring weighting (IPCW) to account for informative loss-to-follow-up, computing weights within the training set. Feature stability will be assessed via bootstrap resampling. We will compute net benefit using decision-curve analysis (assuming equal weight for false positives and negatives). To gauge clinical utility, we will calculate the number needed to treat (NNT) to prevent one composite event under a hypothetical APOL1-targeted therapy: assuming a relative risk reduction of 27% (as reported for inaxaplin), NNT will be derived as the reciprocal of the absolute risk reduction. Comparisons of NNT between APRS-based risk stratification and standard models (KFRE) will be reported. All tests will be two-sided with  $\alpha=0.05$ .

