### 1. Data Preparation

Align predicted risk scores with true survival outcomes.

Apply inverse probability of censoring weights (IPCW) on the test set to adjust for censoring. The IPCW for sample  $i$  at time  $t$  is calculated as:  $IPCW_{i,t} = \frac{1}{\hat{S}(t|X_i)}$  where  $\hat{S}(t|X_i)$  is the estimated probability of being uncensored at time  $t$  given the covariates  $X_i$ .

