### 3. **Weighted Aggregation (for Multiple Time Points)**

If multiple time points are evaluated, compute the weighted mean of each metric using the survival probability at each time point

$$\bar{M} = \frac{\sum_{t=1}^m M_t \cdot \hat{S}(t)}{\sum_{t=1}^m \hat{S}(t)}$$

where  $M_t$  is the metric at time  $t$  and  $\hat{S}(t)$  is the estimated survival probability.

The function returns a dictionary containing the performance metrics at each time point, along with the overall weighted mean metrics if applicable. The pseudo code is as follows:

```

import numpy as np
from sksurv.util import check_y_survival
from sksurv.nonparametric import CensoringDistributionEstimator, SurvivalFunctionEstimator
def cum_metrics(survival_train, survival_test, estimate, times, AUC_sfd=False,
                tied_tol=1e-8):
    test_event, test_time = check_y_survival(survival_test)
    event_shuffle = test_event
    estimate, times = _check_estimate_2d(estimate, test_time, times,
                                         estimator="cumulative_dynamic_auc")

    n_samples = estimate.shape[0]
    n_times = times.shape[0]
    if estimate.ndim == 1:
        estimate = np.broadcast_to(estimate[:, np.newaxis], (n_samples, n_times))
    cens = CensoringDistributionEstimator()
    cens.fit(survival_train)
    ipcw = cens.predict_ipcw(survival_test)
    test_time = np.broadcast_to(test_time[:, np.newaxis], (n_samples, n_times))
    test_event = np.broadcast_to(test_event[:, np.newaxis], (n_samples, n_times))
    times_2d = np.broadcast_to(times, (n_samples, n_times))
    ipcw = np.broadcast_to(ipcw[:, np.newaxis], (n_samples, n_times))
    o = np.argsort(-estimate, axis=0)
    test_time = np.take_along_axis(test_time, o, axis=0)
    test_event = np.take_along_axis(test_event, o, axis=0)
    estimate = np.take_along_axis(estimate, o, axis=0)
    ipcw = np.take_along_axis(ipcw, o, axis=0)
    is_case = (test_time <= times_2d) & test_event
    is_control = test_time > times_2d
    n_controls = is_control.sum(axis=0)
    estimate_diff = np.concatenate((np.broadcast_to(np.infty, (1, n_times)),
                                   estimate))

    is_tied = np.absolute(np.diff(estimate_diff, axis=0)) <= tied_tol
    CU_tp = np.cumsum(is_case * ipcw, axis=0)
    CU_fp = np.cumsum(is_control, axis=0)
    CU_tn = n_controls - CU_fp
    CU_fn = CU_tp[-1] - CU_tp
    CU_n_neg = CU_tn + CU_fn
    CU_n_pos = CU_tp + CU_fp
    tpr_all = CU_tp / CU_tp[-1] # sensitivity

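### The plan does not say which cohort supplies the censoring weights for ARIC and UK Biobank; taken literally, it would use the PMBB training set's

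*Combined protocol and SAP*

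**What the plan says.** Protocol 3.7 lists the weighting among the sensitivity analyses, "to account for informative loss-to-follow-up, computing weights within the training set". SAP section 7, step 1, makes it part of the performance metrics: "Apply inverse probability of censoring weights (IPCW) on the test set to adjust for censoring". The weight there is the reciprocal of a quantity that "is the estimated probability of being uncensored at time" t, given covariates. That text does not say which data the quantity is estimated from.

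The SAP section 7 code does say. It calls "cens.fit(survival_train") and then "ipcw = cens.predict_ipcw(survival_test"). It passes outcomes only, with no covariates, and gives each subject one weight, which is reused at every time point. Cases are weighted, "CU_tp = np.cumsum(is_case * ipcw, axis=0"); controls are simply counted, "CU_fp = np.cumsum(is_control, axis=0").

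SAP 6.4.1 defines the training set as 80% of the APOL1 high-risk PMBB participants. No other training set is defined. External validation in ARIC and UK Biobank is a named objective (protocol section 2).

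On follow-up, protocol 3.6 caps every cohort at 10 years. For ARIC, protocol 3.3 says: "Follow-up (ascertainment of outcomes) is truncated at 10 years from" visit 2. Protocol 3.4 says UK Biobank outcomes come from linked clinical and registry data. Censoring before 10 years is not given for either external cohort.

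**The concern.** A censoring weight repairs the under-observation of late events in the data being analysed, so it has to describe that dataset's own censoring. Within a random PMBB split, the training set is a reasonable source. ARIC and UK Biobank have no training set, yet the only evaluation function requires one. The argument most readily to hand is the PMBB training set.

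If it were used, late external cases would be counted up to about three times to offset losses that occurred in PMBB and perhaps not in the cohort under study. The external time-dependent AUC, and more so PPV, NPV, accuracy and MCC, would then partly reflect PMBB's loss to follow-up. Those figures support the claim that the score transports.

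**Working it through.** **Inputs from the documents.** PMBB training set: 680 participants, 121 composite events, follow-up 7.12 ± 2.91 years. Test set: 7.43 ± 2.78 years, P = 0.21 (Supplementary Table 1). Derivation set: 851 participants, 153 events, mean time to event 6.51 years (SAP section 3). High-risk participants: 314 in ARIC, 204 in UK Biobank (protocol 3.3 and 3.4).

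**Step 1, reproduce the plan's figure.** 121/680 = 17.79%, as printed, so 82.21% of the training set end follow-up without an event. The plan states no weighting result to reproduce.

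**Step 2, PMBB's censoring curve.** None is given, so G(t), the probability of being uncensored at t, was fitted to mean 7.12, SD 2.91 and the 10-year cap under three assumed shapes.

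| Shape | G(5) | G(9) | G(9.9) | 1/G(9.9) |
|---|---|---|---|---|
| Uniform | 0.718 | 0.416 | 0.348 | 2.88 |
| Normal | 0.760 | 0.383 | 0.300 | 3.33 |
| Weibull | 0.730 | 0.409 | 0.347 | 2.88 |

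For the uniform shape (start 1.27 years, width 13.23), the mean capped time is 10 − (10 − 1.27)²/(2 × 13.23) = 7.12, and G(9.9) = 1 − (9.9 − 1.27)/13.23 = 0.348. The fitted medians are 7.8–7.9 years against the SAP's 7.3 for the whole derivation set, so the curves are approximate.

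**Step 3, PMBB weights in a cohort with no censoring before 10 years (assumed).**
- Hazard: 153/(851 × 6.51) = 0.0276 per year.
- True risk at 9.9 years: F = 1 − exp(−0.0276 × 9.9) = 0.239.
- Weighted case mass, uniform G: ∫ h·exp(−hs)/G(s) ds from 0 to 9.9 = 0.359, a mean case weight of 0.359/0.239 = 1.50 where it should be 1.
- Coded event fraction: 0.359/(0.359 + 0.761) = 0.32, against 0.24.
- PPV = Se·p/[Se·p + (1 − Sp)(1 − p)]. With illustrative sensitivity 0.75 and specificity 0.80, PPV is 0.64 at p = 0.32 and 0.54 at p = 0.24.

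**Step 4, the code's formulas on simulated external cohorts.** n = 400,000, t = 9.9 years, no external censoring before 10 years, threshold chosen as in the SAP. Shifts are PMBB weights minus the cohort's own weights, over the three shapes. The effect is the log hazard ratio per SD of score, before and after year 5.

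| Effect | 10-year risk | Own AUC | AUC shift | PPV shift | NPV shift |
|---|---|---|---|---|---|
| Constant 1.3 | 18% | 0.823 | -0.008 | +0.078 to +0.081 | -0.030 to -0.031 |
| Constant 1.3 | 30% | 0.832 | -0.011 to -0.012 | +0.060 to +0.062 | -0.049 to -0.051 |
| Waning 1.6 to 0.8 | 18% | 0.820 | -0.024 to -0.025 | +0.045 to +0.047 | -0.032 to -0.034 |
| Waning 1.6 to 0.8 | 30% | 0.825 | -0.026 | +0.036 to +0.040 | -0.051 to -0.054 |
| Waning 2.0 to 0.5 | 18% | 0.845 | -0.033 to -0.034 | +0.025 to +0.027 | -0.032 to -0.033 |
| Waning 2.0 to 0.5 | 30% | 0.841 | -0.037 | +0.016 to +0.031 | -0.054 to -0.061 |
| Rising 0.8 to 1.6 | 18% | 0.818 | +0.008 | +0.118 to +0.120 | -0.033 to -0.034 |
| Rising 0.8 to 1.6 | 30% | 0.822 | +0.004 | +0.093 to +0.094 | -0.050 to -0.051 |

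A common scale factor in the case weights cancels in the AUC, so only the balance of early and late cases matters there. With an assumed risk of 25% and a constant effect, the sampling SD of the AUC is about 0.028 at n = 314 and 0.034 at n = 204.

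**Step 5, the unweighted controls.** Suppose censoring matches the uniform PMBB curve, so the weights come from the right distribution. Case mass is then correct at 0.239, but controls count only 0.761 × 0.348 = 0.265. The coded event fraction is 0.239/(0.239 + 0.265) = 0.47 against 0.24, and PPV is 0.77 against 0.54. Dividing controls by G(9.9) restores 0.761 and the true fraction. The AUC does not change, because all controls at a given t share the same factor.

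**The case against.** The strongest reply is that nothing states that PMBB outcomes are passed to the function when an external cohort is evaluated. The code is labelled pseudo code, its training argument is generic, and protocol 3.7 speaks of a sensitivity analysis that need not be the weighting in SAP section 7. All of that stands: the carry-over is a literal reading of a silent plan, not a documented act.

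A reader might infer that the protocol and SAP contradict each other, one weighting in training and the other in test. They do not. Estimating the curve in training and applying it to test is one procedure, and the code shows both halves. With similar follow-up in the two PMBB sets, it is acceptable for the AUC there.

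A reader might also infer that ARIC, being truncated at 10 years, has little earlier censoring, so that external validation is shown to be biased. A shared cap says nothing about losses before it, in either direction. No external censoring is the extreme case, used here to bound the effect.

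Nor is it right that the bias disappears only when external censoring matches PMBB's. Step 5 shows the PPV error is larger under matched censoring, because controls are unweighted.

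Finally, the AUC shift is modest. In a separate check with a constant hazard ratio of 3 per SD it was -0.002 at 5 years, -0.004 at 7 and -0.008 at 9.9, and averaging over time points dilutes it. Its sign depends on how the score effect changes over time.

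**Conclusion.** The point holds as an unspecified step with a literal reading that would be wrong wherever external censoring differs from PMBB's. It is not a demonstrated bias.

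If PMBB weights were used in a cohort with no censoring before 10 years, late AUC would shift by about -0.01 under a constant effect, within a range of -0.037 to +0.008. That is mostly below one sampling SD, but it is systematic. PPV would rise by about 0.02–0.12 and NPV fall by about 0.03–0.06. Harrell's C, as named in protocol 3.7, does not use these weights.

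These sizes rest on assumed censoring shapes, assumed score effects, 10-year risks of 18% and 30%, and the absence of early external censoring. Actual ARIC and UK Biobank censoring could make them smaller. The unweighted controls are the larger problem for PPV, NPV, accuracy and MCC, and they affect the PMBB test set too.

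**What to change.** 1. State in protocol 3.7 and SAP section 7 that the censoring distribution is estimated in the cohort being evaluated. For ARIC and UK Biobank, pass that cohort's own outcomes to the fitting call. Keep PMBB training weights for the PMBB test set only.
2. Report each cohort's censoring before 10 years.
3. If PMBB weights were used externally, recompute those time-dependent AUCs and threshold metrics.
4. Weight controls by 1/G(t) when computing PPV, NPV, accuracy and MCC, in every cohort including the PMBB test set. Changing the fitting argument alone does not correct these where there is censoring.
5. In the same edit, reconcile the covariate-conditional weight in the SAP text with the covariate-free estimator in the code, which cannot address the informative loss that protocol 3.7 names.

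Items 1 and 4 cost a sentence, one function argument and one weight term, plus any recomputation. The downside is slightly noisier weights in the smaller external cohorts.

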#### **4. PMBB data source and PMBB-informed operations**

##### **4.1 Study independence and PMBB data source**

The study relies entirely on biospecimens, and coded EHR data obtained from the PMBB (IRB #813913). All operational procedures and governance follow PMBB policies and practices. No new consent was obtained, as the study uses only data and samples already covered under PMBB consent.

##### **4.2 Use of PMBB samples and EHR data**

Cohort derivation relies on biospecimens, and coded clinical data provided by PMBB. Use of PMBB resources for this study follows PMBB's application and review workflow, requires local IRB approval, and is governed by executed Data Use Agreements (DUAs) and/or Material Transfer Agreements (MTAs) that specify minimum-necessary data elements and permitted uses. Any request to access re-identification keys or to perform linkages beyond the provided coded dataset requires additional PMBB approval and execution of a crosswalk/key-file agreement. Analyses of restricted datasets are conducted within approved secure computing environments as required by PMBB.

##### **4.3 Informed consent (PMBB participants)**

All participants whose samples and EHR data are included were originally enrolled in PMBB under PMBB's broad consent framework permitting future IRB-approved research on banked specimens and linked clinical data. If any additional, study-specific prospective enrollment is required, documented written informed consent will be obtained by trained study staff or via an IRB-approved electronic consenting

platform. Consent materials clearly describe study aims, intended uses of samples and data, foreseeable risks, voluntary participation, withdrawal options, and contact information.

#### **4.4 Withdrawal, limits, and participant choices**

Participants may withdraw at any time and will be offered tiered withdrawal options (for example: no further contact; unlinking of identifiers; request for destruction of remaining biospecimens where feasible). The consent will explicitly state that samples or data already released to approved investigators prior to a withdrawal decision generally cannot be recalled and may continue to be used under the terms of the original approvals. Operational handling of withdrawal requests will follow PMBB procedures for documenting and honoring the most recent consent decision.

#### **4.5 Privacy, security, and return of results**

Identifiable information will be stored separately from analytic datasets and maintained within institutional encrypted systems with role-based access controls, multifactor authentication, audit logging, and LIMS-linked specimen tracking. External sharing of data or specimens will occur only under DUAs/MTAs that explicitly prohibit attempts at re-identification; investigators must comply with monitoring and audit requirements and perform analyses within approved secure environments (e.g., Penn Medicine Academic Computing Services or equivalent). Individual research results will not be returned routinely; only analytically validated, clinically actionable findings that meet institutional criteria (confirmed in a CLIA-certified laboratory and accompanied by an IRB-approved return process and counseling when applicable) will be considered for disclosure.

#### **4.6 Governance and compliance**

All requests for sample or data release used by this protocol will be reviewed by the PMBB governance body (and/or the study governance committee) and require IRB-approved protocols and executed DUAs/MTAs. Investigators will provide periodic reports, comply with audits, and promptly report and remediate any data-security incidents in accordance with institutional policy. Cost-recovery fees for sample processing and shipping may apply per PMBB policy.

### **5. PMBB Biospecimen and Procedures**

#### **5.1 Subject Identification Numbers**

This project utilizes samples and health data from participants previously enrolled in the PMBB. Because the PMBB consent explicitly allowed future use of these resources, no new consent process is required. When subjects joined the PMBB, they were given a unique study identifier. All related data and

biospecimens are labeled with this code rather than personal identifiers. Only approved members of the study team can access the secure linkage file that connects codes to individual identities.

## **5.2 Procedures**

Within PMBB, patients from Penn Medicine and community volunteers provide medical history information and blood samples, including both those with kidney disease and healthy controls. Medical data are drawn from participant interviews and the electronic health record. Since participants originally agreed that their samples and data could be used for future studies, no direct re-contact is necessary. Study participants are identified on the basis of phenotype and genotype information already captured in PMBB. Their medical records are then reviewed to clarify disease characteristics, and relevant data are abstracted. All records retain only the minimal required Protected Health Information, which is stored on encrypted and password-protected devices. After abstraction and verification, direct identifiers are removed from analytic files, with a separate linkage file maintained under restricted access.

## **5.3 Biospecimen Workflow**

PMBB biospecimens include blood, DNA, and protein. DNA is isolated and sequenced at certified core facilities, and analyses are performed by qualified bioinformatics staff. Sequencing is carried out using next-generation technologies, followed by computational alignment, filtering, and variant detection to identify potentially relevant rare mutations. Additional genotyping may be performed using standard array-based methods. Genotypes are compared against those of control participants. Plasma aliquots from PMBB are selected based on phenotypic and clinical characteristics and prepared by the PMBB Biospecimen Processing Core. Samples meeting quality and volume requirements are labeled with study-specific identifiers, shipped on dry ice in IATA-compliant packaging, and logged for traceability. Proteomic analyses are performed using high-throughput platforms such as SomaScan and resulting raw and processed data are returned to PMBB for secure storage and downstream analysis. The biospecimens and procedures involved in this project are covered under Penn Medicine Kidney Biobank protocol IRB#857403.

## **6. Ethics and Oversight**

The data and biospecimen used in this study in PMBB were approved by the University of Pennsylvania Institutional Review Board (protocol 815796, 813913 and 857403) and all participants provided informed consent for genetic and EHR research. The validation approved by the University of Pennsylvania Institutional Review Board (protocol 855821). ARIC and UK Biobank investigations were conducted under their respective ethics approvals (ARIC field-center IRBs and UKB ethics; ARIC application MP4524; UKB

application 273810). All procedures will comply with the Declaration of Helsinki and applicable regulations. Participant privacy will be protected by using de-identified data, secure servers with encryption, and HIPAA-compliant protocols. Data use agreements restrict access to authorized personnel, and data transfer (for validation analyses) will employ secure, encrypted channels.

## **7. Subject confidentiality and data security**

### **7.1 Secure data storage**

All data obtained from external database will be stored on encrypted, password-protected Penn Medicine Academic Computing Services servers with access restricted to authorized personnel only. The servers are equipped with state-of-the-art firewalls and intrusion detection systems to safeguard against unauthorized access.

### **7.2 De-identification of data**

The data available through many external databases has already undergone a strict de-identification process to remove personally identifiable information (PII) before being made available to approved researchers. However, in cases where the obtained data is not de-identified, we will implement our own de-identification process using industry-standard techniques such as data masking, pseudonymization, and tokenization. This process will be carried out by trained personnel and will be overseen by the project's data security officer to ensure compliance with Health Insurance Portability and Accountability Act (HIPAA) and other relevant regulations.

### **7.3 Limited data access**

Access to the de-identified data will be granted on a need-to-know basis, with only the principal investigator and key research personnel having direct access. All individuals with data access will be required to undergo training in data security and confidentiality protocols and will sign confidentiality agreements.

### **7.4 Secure data transfer**

When data sharing is necessary for collaboration or validation purposes, we will employ secure file transfer protocols from Upenn (<https://www.isc.upenn.edu/security/secure-share>) and encrypt all data in transit. Data will only be shared with collaborators who have obtained the necessary institutional review board (IRB) approvals and have signed data use agreements outlining the terms and conditions of data access and usage.

